## Abstract

**Background:**

Sexual satisfaction is considered as one of the key factors in assessing a person’s quality of life and the quality and continuity of marital relationships. According to the results of reports in Iran, many couples are dissatisfied with their sexual lives. Sexuality education is one of the important strategies to prevent early sexual problems and improve sexual satisfaction. The aim of this randomized controlled trial is to compare the efficacy of sexual and marital enrichment package using information, motivation and behavioral skills model on sexual satisfaction of new couples in Iran to routine sexual care program that provided at governmental health centers.

**Methods:**

This is a randomized, controlled, superiority trial with two parallel groups. One hundred new couples (*n* = 200) will be recruited and randomized with simple randomization method and a 1:1 allocation. Recruitment will be from governmental health centers and calling on social networks. Couples will be randomized to intervention which will receive Sexual and Marital Enrichment package and control group (routine care at health centers). Couples will be followed up for 4 months. Then primary outcomes (mean score of couples’ sexual information, motivation and behavior skills) and secondary outcome (mean score of couples’ sexual satisfaction) of study will be measured through the online questionnaire.

**Discussion:**

This trial will be examined the impact of the sexual and marital skills training package tailored to the values and norms governing the sexual life of Iranian couples on their sexual satisfaction. If the trial is effective, its results will be presented to policy makers for implementation at national level.

**Trial registration:**

(Iranian Registry of Clinical Trials (IRCT) number): IRCT20181211041926N1. Date of registration: March 2, 2019.

## Plain English summary

Sexual satisfaction is a component of human sexuality that is considered as the ultimate stage of one’s sexual response. According to the results of reports in Iran, many couples are dissatisfied with their sexual lives. Sexuality education is one of the important strategies to prevent early sexual problems and improve sexual satisfaction. The present study is a randomized controlled trial (RCT) that aims to compare the efficacy of sexual and marital skills training package using information, motivation and behavioral skills model on sexual satisfaction of new couples in Iran to routine sexual care program that provided at governmental health centers. The training package includes the 18-h Marital and Sexual Skills Training Workshop, the presentation of the “My Soul Partner” book and sending short messages. Couples in control group receive only the reproductive health care provided at the urban health centers. We expect that sexual and marital skills training package that tailored to the values and norms governing the sexual life of Iranian couples can improve the level of sexual information, motivation and behavioral skills of the couples in intervention group compared to the control group 4 months after the end of intervention. Consequently, we expect to show that training package improves the sexual satisfaction of couples in intervention group compared to the control group.

## Background

Sexual satisfaction in marital relationships is generally considered as one of the key factors in assessing a person’s quality of life and the quality and continuity of marital relationships in particular [1], which is closely associated to the structures related to the quality of marital life, such as communication between couples [2] and marital satisfaction [3]. Sexual satisfaction is a component of human sexuality that is considered as the ultimate stage of one’s sexual response [4]. The concept of sexual satisfaction is divided into two types of satisfaction with sexual activity and emotional satisfaction [5]. In fact, sexual satisfaction is a delightful feeling of individual behavior and interpersonal interactions that is defined as analysis and judgment of one’s own sexual behavior [6].

Sexual satisfaction is correlated with physical and mental health, general happiness, successful social interactions and professional achievements [7]. Sexual satisfaction is also associated with quality of relationship, such as supporting relationships, emotional empathy, physical attractiveness, love, commitment and stability [8]. So that excessive stress caused by sexual dissatisfaction can lead to physical and mental disorders and reduce individual abilities and creativity [9] Hulbert and colleagues state that dissatisfaction with sexual function is closely related not only to divorce but also to some social problems, such as crimes, sexual assault, and mental illnesses. In this regard, Bentovim, quoted from Masters and Johnson, considers the causes of failure of 50% of marriages related to sexual dissatisfaction [10]. According to the results of reports in Iran, many couples are dissatisfied with their sexual lives. Almost 50 to 60% of divorces and 40% of betrayals and covert communication are related to sexual dissatisfaction [9, 11, 12]. One of the problems in the traditional Iranian society is lack of sufficient information on sex and having erroneous attitudes and beliefs about this issue in families, and in particular among new couples. For example, one of the false attitudes that are more common among women is that taking about sex is a sin. This type of attitude prevents a proper response to the legitimate needs of their spouses; so that they not only do not consent to their sexual relationship but also not allow their spouse to enjoy their natural and emotional desires [13]. These shortcomings are often the result of misunderstandings related to sexuality and social and cultural barriers for sex education and lack or low level of quantity and quality of sexual health services [14]. Regarding these issues, one of the important strategies is sexuality education to prevent early sexual problems and promote sexual health. The results of few studies conducted in Iran [15–17] show that sexuality education is effective in improving sexual satisfaction and ultimately marital satisfaction. Given that the sexual education encompasses three domains included of the cognitive (information and knowledge), emotional (emotions, values and attitudes) and behavioral (communication and sexual skills) domains [18]; the Information, Motivation and Behavioral skills model will be used as a theoretical framework in this interventional study.

### Theoretical framework: information–motivation–behavioral skills model

The IMB model conceptualizes psychological determinants of the performance of behaviors that have the valence to destroy, or to modify health status. This model is a useful framework for our study that specifically addresses the sexual information, motivation and behavioral skills needs of young Iranian couples to improve their sexual health. According to the IMB model, information is a fundamental determinant of sexual health behavior performance that can be easily enacted by an individual in his or her social ecology [19]. Information includes specific facts about sexual health promotion, also relative heuristics (plain rules that permit cognitively effortless and automatic– but often incorrect – decisions about whether or not involved in sexual behavior)**.** Third component of information included relatively elaborate implicit theories (complex beliefs that are often incorrect and require cognitive attempt to process in deciding about sexual behaviors). The next structure of IMB model which effects on sexual health promoting behaviors is motivation that include personal motivation (attitudes toward personal performance of sexual health promoting behaviors) and social motivation (social support for enactment of sexual health promotion behaviors). Behavioral skills are an additional principal determinant of IMB models that focuses on an individual’s visual abilities and his or her sensation of self-efficacy [20].

### Objectives and hypothesis

The aim of this randomized controlled trial is to compare the efficacy of sexual and marital skills training package using information, motivation and behavioral skills model on sexual satisfaction of new couples in Iran to routine sexual care program that provided at governmental health centers. It is hypothesized that sexual and marital skills training package will increase sexual information, sexual motivation and sexual behavioral skills of participating couples which will improve sexual satisfaction and ultimately their sexual health compared to control group couples.

### Trial design

This trial is designed as a randomized, controlled, superiority trial with two parallel groups. Randomization will be performed with a 1:1 allocation.

### Study overview

In sexual health interventions using the IMB model, the first step is to focus on elicitation research that aims to empirically identify information deficits, motivational barriers, behavioral skills limitations and assets and general sexual behavior faced in a representative subsample of a target population [20]. For this purpose, semi-structured individual interviews were conducted based on IMB model with 22 heterosexual couples (22 males and 22 females). Based on extracted items from contributing couple interviews, designed the sexual information, motivation and behavioral skills scale (SIMBS) for Iranian couples, and its psychometric properties were confirmed in a sample of 200 couples (400 persons) [21]. SIMBS will be used to assess the initial outcomes of the intervention. The second step involves designing and presenting empirically targeted, conceptually based, population-specific interventions constructed on the basis of elicitation research findings. Therefore, at this stage, a two arms randomized controlled trial will be designed and implemented according to findings from the previous step to address empirically identified deficits in sexual information, motivation and behavioral skills related to sexual satisfaction of couples. The third step is the evaluation of the effect of these interventions after four months follow up to determine whether this interventions have had significant effects on the information, motivation, and behavioral skills as determinants of couples’ sexual satisfaction (Fig. 1- Flow Diagram).

**Fig. 1 Fig1:**
[figure not shown]
Flow diagram of study

## Methods

### Study setting

This study will be conducted in Isfahan city, the capital of Isfahan province in center of Iran.

According to the statistics center of Iran in 2017, the population of Isfahan city was 1,961,260 people. The number of marriages in Isfahan city was 15,409 in 2017 and the number divorces in the same year was 5067. Approximately 64% of divorces occur in the first five years of life [22]. The setting of the study will be at the urban health center in Isfahan city. In urban areas, health centers are the first level of contact between families and governmental health system. Their staff consists of a qualified physician and a team of up to 10 health workers that provide primary, secondary, and tertiary health services to all age groups from birth to death. In Isfahan city, there are 81 health centers in different parts of the city offering numerous health services to clients. This health centers is managed by district health centers, under the supervision of Isfahan University of Medical Sciences.

### Participant selection

#### Inclusion and exclusion criteria

All couples who are referred to health centers of Isfahan city and are willing to participate in the study or volunteer couples that declare their interest through virtual social network to the researcher will be potential participants in the trial if they meet the inclusion criteria. Couples who have a 1 to 5 years marriage history, are over 18 years old, have at least a degree in secondary schools, living in Isfahan city, do not have any severe mental illness (according to history taking by the main researcher (FB)), both couples express agreement to participate in the study and have a cell phone will be eligible to enter the study. The first criterion is the definition of new or recently married couples [23]. Couples who meet the inclusion criteria but have been divorced or have severe marital problems or husband or wife is unwilling to participate in the study will be excluded from the trial.

#### Recruitment

Informing couples will be done through an invitation entitled “Sexual Relationships Enrichment of New Couples” as a poster that will be installed on the bulletin boards at each of the health center. At the same time, the invitation will be published online on the virtual social network. In health centers, one of the health providers will also be trained about the goals of study and the sampling method. The couples who are eligible to study will be identified by trained health providers and the objectives and conditions of study will be explained to them. Couples can also contact to research team through social network that will be screened for eligibility. Additional information will be given to eligible couples who agree to participate in the trial and their contact numbers will be recorded for inviting in the meetings. All eligible couples who are willing to participate in the study will sign a written consent in Persian language before entering to the trial. The participation will be voluntary and they could withdraw from the study at any time.

#### Randomization

In this study, a simple randomization method will be used. The unit of randomization will be a couple. Firstly, eligible couples will be assigned randomly to either the intervention or the control group according to the Random Number Table, and then the randomization will continue until the balance is established in terms of the size of the groups. In order to ensure allocation concealment, the central randomization method will be used so that a random sequence was given to the original researcher at one of the centers and the samplings of couples in other centers are done simultaneously. Other colleagues at other centers will contact the researcher through the telephone and ask questions about the random allocation of the couple to the special group.

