### Sample size

According to the results of studies conducted in Iran about the effect of sexual health education on sexual satisfaction of couples [14], the maximum significant difference was found in sexual satisfaction score between intervention and control groups was 5.38. A sufficient sample size to detect the maximum difference between the intervention and control groups in the sexual satisfaction score with 80% of the power at significant level α = 0, 05 and considering the rate of loss 5% will be 200 people. Thus, 50 couples (*n* = 100) will be assigned to the intervention group and 50 couples (n = 100) will be assigned to the control group.

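### Simple randomisation continued until the arms balance does not fit the fixed 50 couples per arm, and the sequence is not concealed from the researcher who holds it

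*Protocol article*

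**What the plan says.** On the method, the Randomization section states "In this study, a simple randomization method will be used" and "The unit of randomization will be a couple". Couples are allocated from a random number table, and "then the randomization will continue until the balance is established in terms of the size of the groups". Trial design says "Randomization will be performed with a 1:1 allocation". Sample size fixes the arms: 50 couples go to the intervention, and "50 couples (n = 100) will be assigned to the control group".

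On concealment, the Randomization section claims a central method in which "a random sequence was given to the original researcher at one of the centers". Colleagues at the other centres telephone that researcher to learn each couple's group.

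On who decides entry, the Inclusion and exclusion criteria section has severe mental illness judged "according to history taking by the main researcher". The Recruitment section has trained health providers identify eligible couples at the centres. For the online route it says "Couples can also contact to research team through social network that will be screened for eligibility", without saying who does the screening.

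On contact and access, Outcome assessment has the main investigator contact couples at baseline and at four months, and lets only that person view the responses. Follow up and data collection gives the same contact task to the original researcher. Baseline questionnaires come before assignment.

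**The concern.** There are two separate problems.

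First, simple randomisation does not produce a preset equal split, so the balance clause must add something to it. The text does not say what. It could mean recruiting on until the arms happen to be equal, or closing an arm once it is full and sending the remaining couples to the other. The first leaves the sample size open. The second makes the end of the sequence deterministic.

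Second, concealment is meant to keep the next allocation from anyone who can influence whether a couple enters. Here the sequence sits with a study researcher who contacts participants at baseline and who appears also to judge an entry criterion.

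What is at stake is selection at entry. Couples know whether they attend six workshops, and the outcomes are self-reported. The planned t-tests and ANCOVA cannot correct for selection on traits that were not measured, such as motivation or marital strain.

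**Working it through.** **Inputs.** 100 couples, 50 per arm (Sample size); ratio 1:1 (Trial design); unit of randomisation the couple, method simple (Randomization). The plan's totals agree with each other: 2 arms × 50 couples × 2 partners = 200 people. The power calculation behind the 200 cannot be reproduced because no standard deviation is given, but nothing below depends on it.

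**1. Does simple randomisation give 50:50?**
P(exactly 50 of 100) = C(100,50)/2^100 = 0.0796, or about 8%. The chance of a split of 45:55 or more uneven is 0.37.

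**2. Reading A: an arm closes at 50 and the rest fill the other arm.**
Let T be the number of couples left when the first arm reaches 50. Their allocation is certain.
- P(T = t) = 2 × C(99−t, 49)/2^(100−t), for t = 1 to 50.
- Mean of T = 100 × 0.0796 = 7.96; median 7; 90th percentile 16.
- P(T ≥ 5) = 0.68 and P(T ≥ 10) = 0.34.

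**3. Reading B: keep randomising past 100 until the arms are equal.**
No allocation is forced, but the sample is open-ended. In 20,000 simulated trials the median was 96 extra couples, and 49% of trials needed more than 100 extra. This does not fit a trial of 100 couples.

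**4. Reading C: a list made in advance with 50 of each, in random order.**
The last couple is always determined. Each of the other 49 couples in the same arm falls after all 50 of the opposite arm with probability 1/51. The expected forced run is 1 + 49/51 = 1.96, or about 2 couples. This gives equal arms with little predictability, but it is not simple randomisation and needs no balance clause.

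**5. Who holds the list? The sections side by side.**
- Randomization: the original researcher has the sequence and answers the telephone.
- Follow up and data collection: the original researcher contacts participants at baseline and four months.
- Outcome assessment: the main investigator does that same contacting and alone views the responses, including the baseline answers given before assignment.
- Inclusion and exclusion criteria: the main researcher takes the history that settles the mental illness criterion.

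The identical contact task links the original researcher to the main investigator, and the main researcher is most naturally the same person. If so, one person knows the next allocation, can see a couple's baseline scores and judges an entry criterion. No sentence says this outright.

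**The case against.** A reader might infer that allocation is not concealed at all. The documents do not support that. The telephone step keeps the sequence from colleagues at the other centres, and health providers there identify eligible couples without seeing it. Concealment fails for the list holder only.

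A reader might also take it as stated that the person who screens sees every next allocation. That too goes beyond the text. The shared identity is inferred, the main researcher is named for one criterion only, and nobody is named as judging severe marital problems or as screening the online volunteers. What stands is that the list holder is a study researcher who contacts participants at baseline and probably judges eligibility.

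On predictability, the figure of 8 couples belongs to reading A; with a pre-made 50+50 list it is about 2. In either case a caller could use the forced tail only by knowing the running totals across centres, and nothing gives callers those totals. Reading B conflicts with the fixed 100 couples, so it shows that the clause fails as written rather than a likely outcome.

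It is also fair that permuted blocks have determined ends of their own: about 25 × 1.33 = 33 allocations per 100 couples with blocks of 4, and about (100/6) × 1.5 = 25 with blocks of 6. Blocks therefore help only if block sizes and list are hidden from recruiters. Equal arms are not essential either: a 45:55 split keeps 4 × 0.45 × 0.55 = 99% of the efficiency.

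Finally, the plan already puts eligibility, consent and baseline before allocation. That stands, and it needs keeping rather than adding.

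**Conclusion.** The point holds in a limited form. The method contradicts itself: simple randomisation reaches the required 50:50 split with probability only 0.08, and the balance clause does not say how the gap is closed. If an arm closes at 50, about 8 of 100 allocations are certain on average, and 10 or more in 34% of trials. Those figures assume independent 1:1 draws and an arm that shuts when full, and they matter only for someone who knows the running totals.

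Concealment works for the telephoning centres and fails for the list holder. How serious that is depends on whether the original researcher, main investigator and main researcher are one person, which is probable from matching duties but not stated. If the roles differ, the sequence still rests with a researcher who contacts participants at baseline, and the contradiction in method is unaffected. The stronger conclusions, that nobody is blind to the next allocation or that all allocations are known to whoever screens, do not follow from the documents.

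**What to change.** 1. Delete the clause about continuing until the groups balance and state one method. Either use a pre-generated 1:1 list for 100 couples, for example in permuted blocks of randomly varying size concealed from recruiters, or use truly simple randomisation of 100 couples with unequal arms accepted. If the second is chosen, the statement of exactly 50 couples per arm must be reworded.
2. Have the list held by an existing team member with no role in eligibility, enrolment or participant contact, or use sequentially numbered opaque sealed envelopes. The telephone line can stay.
3. Keep the planned order of eligibility, consent and baseline before allocation, and say that it applies to all couples, including those from social networks.
4. Use one term for each role, so that a reader can see who holds the list and who judges eligibility.

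The cost is small: a new list, and the telephone duty moves to another person. The article does not show that a team member without those duties is available; if there is none, the envelopes serve. Blocks are slightly less random than unrestricted allocation. The total of 100 couples does not change.
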